## Abstract

**Background:**

Falls are one of the world’s top 10 risks associated with disability in people older than 60 years. They also represent more than two-thirds of adverse events in hospitals, mainly affecting patients older than 65 years. Physical activity is a central intervention in fall prevention for older people. Whatever the details of the prevention strategy that is adopted (ie, how a mono- or multifactorial intervention is evaluated, the category of person the intervention targets, and where it is used), it is important to ensure that the proposed intervention is feasible and usable for the patient and the health care team.

**Objective:**

The primary objective is to study the usability of carrying out a physical activity intervention, including 3 types of exercises, in older patients hospitalized in a geriatric acute care unit and categorized according to 3 fall risk levels: low, moderate, and high. The secondary objectives are to determine the difficulty of the physical exercise for patients with different fall risk levels, to study the health care team’s perceptions of the intervention’s feasibility, and to study the benefits for patients.

**Methods:**

This is an open-label, unicenter, nonrandomized, usability prospective clinical trial. The intervention tested is a daily physical activity program. It consists of 3 types of physical exercise: staying out of bed for at least 3 hours, performing balance exercises while standing for 2 minutes, and the Five Times Sit to Stand transfer exercise. These exercises are carried out under the supervision of the health care team. Fall risk in the patients is classified with the Brief Geriatric Assessment tool. The exercise program starts on the second day of hospitalization after inclusion in the study. Patient assessment continues until the last day of hospitalization or the 20th day of hospitalization, whichever is earlier. For each fall-risk group and each type of exercise, the intervention will be defined as usable if at least 80% of the participants complete 75% or more of the exercises (ie, the ratio between the number of days when the patient completes a type of exercise and the total number of hospitalization days). The perceived feasibility by the health care team is measured with 2 scales, measuring perceived difficulty and time spent with the patient. The intervention benefit is evaluated using the performance of the Five Times Sit to Stand test before and after the intervention.

**Results:**

The first patient was recruited on March 16, 2015. The study enrolled 266 patients, including 75 with low fall risk, 105 with moderate risk, and 85 with high risk.

**Conclusions:**

We have not yet analyzed the results, but our observations suggest that the usability of each type of exercise for a given patient will depend on their fall risk level.

**Trial Registration:**

ClinicalTrials.gov NCT02393014; https://clinicaltrials.gov/ct2/show/NCT02393014

**International Registered Report Identifier (IRRID):**

DERR1-10.2196/32288

## Introduction

### Context

Falls are one of the world’s top 10 risks for causing disability in people aged older than 60 years [1]. More than two-thirds of adverse events in hospitals are falls, mainly affecting patients older than 65 years [2,3]. Falls are accompanied by multiple physical and psychological consequences that cause disability, increased length of stay, and increased cost of care [2,3]. Fall risk factors may be classified as (1) biological (related to disease or aging), (2) associated with daily behavior (related to eating, being active, dressing, and other habits), (3) social and economic (related to social isolation, poverty, financial resources, or lack of access to health care), and (4) environmental, including the local environment (building entrances, lack of handrails, type of furniture) and the climate [4]. The management of falls relies on various strategies: avoiding the first fall, fast intervention and treatment when a fall occurs, and preventing additional falls [5].

Physical activity is a central intervention in fall prevention programs for older persons. It contributes to the restoration and maintenance of muscle function and tone, joint mobility, improved balance, and walking ability [5-8]. Physical activity recommendations for older people [9], particularly frail patients at risk of falling [5,6], include moderate-intensity physical activity for 15 to 30 minutes as often as possible during the week; exercise programs based on balance, strength, and gait; group exercise supervised by a professional, to take into account the physical capabilities and health profile of older persons; and regular review of progression to adjust the exercise prescription as appropriate. Recommendations also include multicomponent interventions [10]. It has been shown that multicomponent interventions, which combine physical activity and corrective actions, decrease the annual incidence of falls by 10% to 30% [6,7].

Staying active prevents functional disabilities, particularly in older patients who are hospitalized [11]. These patients quickly lose their ability to perform daily acts by themselves, such as getting up from a low position or walking, causing them to become severely sedentary [6-8,12]. In this context, an intervention can be considered a secondary or tertiary prevention (ie, taking place after confirmation of early-stage risk factors, such as frailty or a history of falls) rather than a primary prevention (ie, before the onset of the disease) [13].

Considering (1) the preventive strategy adopted (ie, the evaluation associated with a mono- or multicomponent intervention), (2) the category of person targeted, and (3) where the intervention takes place (ie, in a home, institution, or hospital), it is important to ensure that the proposed intervention is feasible and usable for the person or the group of people concerned. This is particularly important considering the frailty of older inpatients and the availability of the health care team.

### Hypothesis

We hypothesize that in the geriatric acute care unit of a university hospital, it will be possible to carry out a physical activity intervention based on the physical acts of daily life, focusing on strengthening the lower-limb muscles and improving postural balance.

### Objectives

#### Primary Objective

The primary objective is to study the usability of carrying out a physical activity intervention including 3 types of exercise in older inpatients at a geriatric acute-care unit and categorized according to 3 fall risk levels: low, moderate, and high.

#### Secondary Objectives

There are 3 secondary study objectives. Secondary objective A will be to determine the difficulty level of the physical exercises in each fall risk group and analyze the usability of the intervention in each group to determine the best intervention modality for each group. Secondary objective B will be to determine the health care team’s perception of the difficulty of carrying out the intervention and analyze their perceptions with 2 scales. Secondary objective C will be to examine the effects of this physical activity intervention on the patients’ lower-limb strength, comparing their ability and time to perform the Five Times Sit to Stand (FTSS) test before (measured during a clinical assessment) and after the intervention (on the last day of hospitalization or the 20th day of hospitalization, if the patient is still hospitalized).

## Methods

### Design

This is an open-label, unicenter, nonrandomized, usability prospective clinical trial. There is no comparator group (ie, no control group). Figure 1 illustrates the trial design and Table 1 summarizes the timing of the trial. The intervention tested in this study is a physical activity intervention based on the physical acts of daily life that focuses on strengthening the lower-limb muscles and improving postural balance. It consists of 3 types of physical exercise that can be adapted to the fall risk level. It is offered to 3 categories of hospitalized patients, classified according to their risk of falling: low, moderate, and high. It is carried out from the second day of hospitalization after an assessment of the patient’s risk of falling until the last day of hospitalization or the 20th day of hospitalization if the patient is still hospitalized. In summary, this study consists of an inclusion visit, a physical activity program performed daily until the 20th day of hospitalization, and an end-of-study visit.

**Figure 1 figure1:**
[figure not shown]
Trial flow chart. FTSS: Five Times Sit to Stand.

**Table 1 table1:** Timeline of the study.

	Enrollment and allocation	Follow up	Study end (last day of hospitalization or 20th day, whichever is earlier)
Inclusion and exclusion criteria applied	✓		
Informed consent obtained	✓		
Group assignment	✓		
Clinical assessment	✓		✓
Five Times Sit to Stand test	✓	✓^a^	✓
Pain	✓	✓^a^	✓
Physical activity intervention		✓^b^	✓

^a^Only measured on the sixth day of follow up.

^b^Performed daily.

### Planned Eligibility Criteria

#### Inclusion Criteria

Patients are included if they are at least 65 years old, hospitalized in a geriatric acute-care unit, and have no contraindications to physical activity, standing, or sitting. Patients must also be covered by a social security scheme and have given and signed an informed consent form to participate in the study (informed consent can also be obtained from a trusted person or legal representative, as appropriate).

#### Exclusion Criteria

Patients are excluded if their hospitalization was shorter than 3 days, they were participating in a concomitant therapeutic trial, or if they were under any of the 3 French civil protection measures: curatorship, guardianship, and safeguard of justice.

### Intervention

This intervention follows the main principles of the latest French National Authority for Health (HAS) recommendations on the prevention of falls in older people [11]. Each fall risk group of participants will receive a physical activity intervention, carried out once a day, consisting of 3 types of exercise. In exercise 1, the participant must stay out of bed for at least 3 hours. This length of time prevents acute postural disorders that increase the risk of falling; these can occur when older patients are bedridden for too long. In exercise 2, the participant stands in static equilibrium for 2 minutes in front of a chair, holding the back of the chair. Depending on the participant’s abilities, the exercise is done standing on one or both feet. Exercise 3 requires the participant to switch from sitting on a chair to standing 5 times (this is similar to the FTSS test but is not timed). Depending on the patient’s abilities, the exercise is done with or without physical assistance.

This daily intervention is carried out starting on the day after informed consent is obtained from patients fulfilling the selection criteria. It is carried out under the supervision and monitoring of the health care team, specifically nurses and nursing assistants.

### Assessments

#### Fall Risk Assessment

The Brief Geriatric Assessment (BGA) tool [14] is used to assess fall risk level. It consists of six items, coded as binary variables: (1) age (over or under 85 years), (2) gender (male or female), (3) number of medications taken daily (over or under 5), (4) history of falls during the past 6 months (yes or no), (5) cognitive level, assessed as the ability to identify the month and year (yes or no), and (6) use of home help services (yes or no). The BGA tool classifies patients into 3 fall risk levels using an algorithm that consider criteria 4 and 5 as major fall risks and criteria 1, 2, 3, and 4 as minor fall risks: group 1, low fall risk; group 2, moderate fall risk; and group 3, high fall risk. The BGA is used by the health care team as part of usual care.

#### Clinical Assessments

Clinical assessments are performed at inclusion and during follow up (Table 1). Except for the FTSS test, which is applied during follow up and at the end of the study, all clinical assessments are carried out as part of usual care. Clinical data are collected from the computerized patient medical file or directly from the participant if the data have not yet been added to the file.

The clinical assessment at inclusion will include the reason for hospitalization (including organ failure, musculoskeletal disorders or falls, neuropsychiatric disorders, medicosocial problems, or other causes); age and gender; anthropometric data (ie, weight and height); body mass index (kg/m^2^); and the Mini-Mental State Examination (MMSE) [15] score. The MMSE is used to assess cognitive function. It consists of 30 questions in 5 sections (orientation, memory and recall, attention, calculation, and language), with a final score graded out of 30 points. In the absence of memory complaint, (self-reported or non–self-reported), a final score between 27 and 30 indicates the probable absence of a cognitive disorder.

Clinical assessments at inclusion and during follow up will include the use of psychotropic drugs (eg, antidepressants, benzodiazepines, hypnotics, and neuroleptics); the number of different therapeutic classes of drugs taken; the FTSS test; and the patient’s overall pain, assessed using a verbal 6-point scale: “no pain,” “low pain,” “moderate pain,” “high pain,” “extreme pain,” and “not assessable.” The pain assessment is used to verify changes in pain level during hospitalization. The FTSS test measures a patient’s physical transfer ability. The test is to stand up from a chair 5 times as quickly as possible without pushing off. Performance is measured in seconds, from the initial seated position to the final seated position after having completed standing up 5 times. A time longer than 15 seconds is abnormal and is associated with physical and cognitive impairment [16].

### Monitoring of the Implementation of the Physical Activity Program

Nurses are in charge of keeping a physical activity monitoring form up to date, which is also digitized in the computerized patient medical file and added to the case report form. This form includes the following information: date of daily physical activity session; level of completion for each type of exercise; reasons why the daily objectives were not reached during the session; perceived feasibility of the daily session by the caregiver; time spent by the caregiver conducting the daily session; and occupational category of the caregiver who supervised the daily session, including nursing assistant, nurse, physiotherapist, occupational therapist, paramedical student, and second-cycle (equivalent to a master’s degree in medical sciences) medical student.

### Outcomes

#### Primary Outcome Measure

The primary outcome measure is the number of participants in each fall risk group who complete 75% or more of the physical activity program for each type of exercise during hospitalization. For each type of exercise, success is quantified daily as follows: for exercise 1, the participant was able to stay out of bed for at least 3 hours; for exercise 2, the participant stood in static balance for at least 2 minutes in front of the chair, holding the back of the chair; and for exercise 3, the participant switched from sitting on a chair to standing at least 5 times. The percentage represents the ratio between the number of days when the patient successfully completes a type of exercise and the total number of days of hospitalization. For each fall risk group and each type of exercise, the intervention will be defined as usable if at least 80% of the participants complete at least 75% of the exercise. These thresholds have not been scientifically validated.

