## Results

The first participant was included on March 16, 2015. We preselected 278 patients, of whom 266 enrolled in the study (low fall risk group: 75 patients, moderate fall risk group: 105 patients, and high fall risk group: 85 patients).

We will not include more patients. We have not yet analyzed the results, but our first impression is that the high fall risk group was only able to complete exercise 1 (ie, staying out of bed for at least 3 hours daily), the moderate fall risk group was able to complete exercises 1 and 2 (ie, they could also complete the 2-minute balance exercise), and the low fall risk group was able to complete all the physical activity exercises.

Despite this first impression, the program does not seem to have been perceived as difficult or time consuming by the health care team. Detailed statistical analyses will make it possible to explore in detail the results of this study and to meet its objectives.

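### Counted in calendar days, the primary 75% ratio includes at least one hospital day on which no session was possible, which pulls short stays toward failure

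*Protocol article*

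**What the plan says.** The Primary Outcome Measure section opens with the number of patients in each fall risk group who "complete 75% or more of the physical activity program for each type of exercise during hospitalization". It then defines the percentage as "the ratio between the number of days when the patient successfully completes a type of exercise and the total number of days of hospitalization". The abstract (Methods) gives the same denominator: "the ratio between the number of days when the patient completes a type of exercise and the total number of hospitalization days". An exercise is called usable in a risk group when 80% or more of that group's patients reach 75%.

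Three places fix when sessions can happen:
- Design: "It is carried out from the second day of hospitalization after an assessment" of fall risk.
- Intervention: "This daily intervention is carried out starting on the day after informed consent is obtained from patients fulfilling the selection criteria".
- Table 1 ticks the intervention under follow up and under the column headed "Study end (last day of hospitalization or 20th day, whichever is earlier"), but not under enrollment.

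On short stays, the Exclusion Criteria say: "Patients are excluded if their hospitalization was shorter than 3 days". A 3-day stay is therefore eligible. The Results section gives the enrolled groups as "low fall risk group: 75 patients, moderate fall risk group: 105 patients, and high fall risk group: 85 patients".

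**The concern.** The opening sentence of the outcome promises a share of the program, but the ratio that follows measures a share of the hospital stay. A day before the program starts enters the denominator and can never enter the numerator, so it has the same effect as a missed session. The shorter the stay, the more that day weighs.

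This matters because the 75% pass decides the primary outcome through a fixed 80% cut for each group and exercise. The same result feeds secondary objective A, which picks the exercises suited to each risk group. The Discussion makes verified usability one of the conditions for the planned larger study. A pass rate that depends partly on length of stay and on the timing of consent would blur what it is meant to show, namely whether patients can do the exercises.

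**Working it through.** No figure in the plan depends on this ratio. The sample size is described as empirical, so there is nothing to reproduce first. The check is on the rule itself.

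**Inputs.** L is the stay in calendar days, with admission as day 1. c is the hospital day of consent. The first session is on day c + 1 (Intervention) and the last on day L or day 20, whichever is earlier (Design, Table 1). The article gives neither L nor c, so c = 1 is taken as the most favorable case and c = 2 and 3 as variations.

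**Best attainable ratio, L up to 20.** A patient who completes every possible session scores (L − c)/L. This reaches 0.75 only if L ≥ 4c.
- c = 1: L = 3 gives 2/3 = 66.7% (fails); L = 4 gives 3/4 = 75.0%; L = 7 gives 6/7 = 85.7%; L = 20 gives 19/20 = 95.0%.
- c = 2: L = 7 gives 5/7 = 71.4% (fails); L = 8 gives 6/8 = 75.0%.
- c = 3: no stay under 12 days can pass.

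**Successful sessions needed, c = 1.** The published ratio needs 0.75 × L, rounded up. A program-day ratio needs 0.75 × (L − 1), rounded up. L − 1 sessions are possible.

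| Stay L | Possible | Published ratio | Program-day ratio |
|---|---|---|---|
| 3 | 2 | 3 (unattainable) | 2 |
| 4 | 3 | 3 | 3 |
| 5 | 4 | 4 | 3 |
| 6 | 5 | 5 | 4 |
| 7 | 6 | 6 | 5 |
| 8 | 7 | 6 | 6 |
| 10 | 9 | 8 | 7 |
| 12 | 11 | 9 | 9 |
| 20 | 19 | 15 | 15 |

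From 3 to 20 days the difference is 0 at L = 4, 8, 12, 16 and 20, and 1 at every other length.

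**Direction.** For s successful days, s/(L − c) is never smaller than s/L. A patient who passes under the published ratio therefore always passes under the program-day ratio. Disagreement can run only one way.

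**Stays beyond day 20.** The ratio states no cap. Read literally with c = 1, L = 25 gives at most 19/25 = 76.0% and L = 26 gives 19/26 = 73.1%, which cannot pass.

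**Counting convention.** The Design section numbers days ordinally, which fits calendar days, but no rule is stated. If the denominator is counted in nights, a day-1 consent gives (L − 1)/(L − 1) = 100% and the effect disappears. If the 3 days in the Exclusion Criteria are elapsed days, the shortest stay covers 4 calendar days and can reach 3/4 = 75%.

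**Link to the 80% rule.** Passes needed are 0.8 × 75 = 60, 0.8 × 105 = 84 and 0.8 × 85 = 68. A group is therefore not usable once 16, 22 or 18 patients fail.

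**Illustration only.** Assume c = 1 and independent sessions, each completed with probability p. The chance that a patient passes, published versus program-day ratio, is:
- 6-day stay: 44% vs 84% (p = 0.85), 59% vs 92% (p = 0.90), 77% vs 98% (p = 0.95).
- 8-day stay, p = 0.90: 85% under both.
- 10-day stay, p = 0.90: 78% vs 95%.
- 20-day stay, p = 0.90: 97% under both.

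**The case against.** The strongest reply is that the ratio is loose shorthand in a condensed article. The outcome is introduced as a share of the program. The abstract limits assessment to the time from program start to discharge or day 20 just before it gives the ratio. Completion is recorded on a form dated by session. On that reading only the wording needs repair, and the missing day-20 cap is probably the same shorthand. This has weight, but the all-days denominator is stated explicitly in two places and nothing in the article limits it. It is a stated rule, not a detail left to another document.

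The second reply is that the effect may be small. This largely stands. With day-1 consent it is one session at most. At 4 days the program-day ratio allows no miss either, so the strictness there does not come from the denominator. The sixth-day sit-to-stand test and the day-20 limit suggest that stays of about a week or more were expected. For 3-day stays alone to sink a group, about 21% of it (16/75, 22/105 or 18/85) would need that minimum stay, and nothing in the article suggests so. The 6-day illustration lies near the largest gap. Independence between sessions is also doubtful: if patients complete nearly all or very few sessions, one session rarely changes the result outside 3-day stays.

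The third reply is that a stricter denominator is conservative in a single-arm study and is common to all three exercises. That is true within a group. It does not protect comparisons between risk groups if stay or consent timing differs among them.

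**Conclusion.** The point holds conditionally. If hospitalization days are calendar days, the published ratio counts at least one non-program day against every patient and does not measure the program share that the same section sets as its target. With day-1 consent, an eligible 3-day stay cannot pass. Stays of 5, 6 and 7 days must be perfect where a program-day ratio would allow one miss. Up to day 20 the gap is at most one session, and it is nil at 4, 8, 12, 16 and 20 days. Later consent makes it larger, since a stay shorter than 4c days cannot pass, but the article does not report when consent was obtained.

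A reader might infer that the usability results are materially biased, or that a day is lost for every patient whatever the counting convention. The document supports neither. The direction is known (toward not usable, most for short stays), but the effect on the 80% decision cannot be calculated without the distributions of stay and consent day. With nights as the denominator and day-1 consent there is no effect. Nor does it follow that the published definition should simply be replaced: enrollment has closed, and the Results section already gives impressions by group and exercise.

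**What to change.** Before analysis:
- State the day-counting convention, and word the start rule the same way in the abstract, Design and Intervention.
- Define a program-day ratio whose denominator runs from the day after consent to discharge or hospital day 20, whichever is earlier.
- Report the 80% usability conclusion under both the published ratio and the program-day ratio, for each of the 3 × 3 = 9 combinations of risk group and exercise. Describe any combination where the two disagree as dependent on the denominator.
- Declare the program-day ratio as added after enrollment closed.
- Tabulate consent day and number of program days by risk group, so that readers can see how many patients could be affected.

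The cost is a small amount of extra analysis, with no new patients or visits. It needs admission, consent and discharge dates, assumed available from the consent form and hospital file; daily completion is already on the monitoring form. The drawback is a late addition in the direction favorable to usability, which is why the published ratio must stay visible beside it.
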